# The CARDIA-trial protocol: a multinational, prospective, randomized, clinical trial comparing transthoracic esophagectomy with transhiatal extended gastrectomy in adenocarcinoma of the gastroesophageal junction (GEJ) type II

**DOI:** 10.1186/s12885-020-07152-1

**Published:** 2020-08-20

**Keywords:** esophageal adenocarcinoma, gastroesophageal junction, Siewert type II, cardia carcinoma, esophagectomy, gastrectomy

## Abstract

**Background:**

Adenocarcinoma of the gastroesophageal junction (GEJ) Siewert type II can be resected by transthoracic esophagectomy or transhiatal extended gastrectomy. Both allow for a complete tumor resection, yet there is an ongoing controversy about which surgical approach is superior with regards to quality of life, oncological outcomes and survival. While some studies suggest a better oncological outcome after transthoracic esophagectomy, others favor transhiatal extended gastrectomy for a better postoperative quality of life. To date, only retrospective studies are available, showing ambiguous results.

**Methods:**

This study is a multinational, multicenter, randomized, clinical superiority trial. Patients (*n* = 262) with a GEJ type II tumor resectable by both transthoracic esophagectomy and transhiatal extended gastrectomy will be enrolled in the trial. Type II tumors are defined as tumors with their midpoint between ≤1 cm proximal and ≤ 2 cm distal of the top of gastric folds on preoperative endoscopy. Patients will be included in one of the participating European sites and are randomized to either transthoracic esophagectomy or transhiatal extended gastrectomy. The trial is powered to show superiority for esophagectomy with regards to the primary efficacy endpoint overall survival. Key secondary endpoints are complete resection (R0), number and localization of tumor infiltrated lymph nodes at dissection, post-operative complications, disease-free survival, quality of life and cost-effectiveness. Postoperative survival and quality of life will be followed-up for 24 months after discharge. Further survival follow-up will be conducted as quarterly phone calls up to 60 months.

**Discussion:**

To date, as level 1 evidence is lacking, there is no consensus on which surgery is superior and both surgeries are used to treat GEJ type II carcinoma worldwide. The CARDIA trial is the first randomized trial to compare transthoracic esophagectomy versus transhiatal extended gastrectomy in patients with GEJ type II tumors. Several quality control measures were implemented in the protocol to ensure data reliability and increase the trial’s significance. It is hypothesized that esophagectomy allows for a higher rate of radical resections and a more complete mediastinal lymph node dissection, resulting in a longer overall survival, while still providing an acceptable quality of life and cost-effectiveness.

**Trial registration:**

The trial was registered on August 2nd 2019 at the German Clinical Trials Register under the trial-ID DRKS00016923.

## Background

Adenocarcinomas of the gastroesophageal junction (GEJ) are located at the borderline of the stomach and esophagus. GEJ tumors show an increase in incidence in the Western world. In the Netherlands for example, the incidence of esophageal cancer more than doubled in a period of less than 20 years [1]. Approximately 27% of patients with a GEJ tumor, suffer from a GEJ Siewert type II ‘true’ cardia carcinoma, meaning that the midpoint of the tumor is between ≤1 cm proximal and ≤ 2 cm distal from the GEJ (see Fig. 1) [2]. Earlier studies suggested that these tumors can have two distinct etiologies (esophageal and gastric) [3], whereas more recent genetic analysis showed that the origin may be similar [4]. Regardless of the hypothesized origin, given that the incidence of GEJ cancer has risen by up to 350% in Western Europe since the 1970’s, determination of optimal treatment is imperative to improve patient outcome [5].

**Fig. 1 Fig1:**
[figure not shown]
Endoscopic classification of GEJ type II tumors according to the Siewert classification of GEJ cancer. Type II tumors have their midpoint 1 cm above to 2 cm below the cardia.

Successful surgery is the cornerstone of multimodal treatment leading to a 5-year survival rate of 40–50% [6, 7]. There is an ongoing controversy about the optimal surgical approach for Siewert type II tumors. In order to provide the best, intentionally curative, treatment in patients with GEJ tumors, a radical resection of the tumor needs to be combined with removal of adjacent lymph nodes. This can be achieved by two surgical approaches: a transthoracic esophagectomy or a transhiatal extended gastrectomy. Two recent international surveys on this topic show that the worldwide preferred surgical approach for Siewert type II tumors was extended gastrectomy in 66% of respondents, followed by esophagectomy in 27% [8]. Although extended gastrectomy was found in some studies to be associated with a higher quality of life [9, 10], oncological outcome may be compromised with a higher rate of microscopic neoplastic invasion of the circumferential resection margin and less lymph node metastases resected [11]. To date, the superior surgical approach concerning survival, oncological outcome and quality of life remains unclear, as only retrospective studies are available, showing ambiguous results. This lack of level 1 evidence translates to the lack of consensus in current clinical practice worldwide.

## Methods

### Objective

The objective of this study is to compare transthoracic esophagectomy versus transhiatal extended gastrectomy in patients with resectable Siewert type II GEJ adenocarcinoma. The primary efficacy endpoint is overall survival and key secondary endpoints are complete resection (R0), post-operative complications, number and localization of tumor infiltrated lymph nodes at dissection, disease-free survival, quality of life and cost-effectiveness. It is hypothesized that esophagectomy allows for a higher rate of radical resections and a more complete mediastinal lymph node dissection resulting in a longer overall survival, while providing an acceptable quality of life and cost-effectiveness.

### Study design

This study is a multinational randomized clinical trial comparing the two surgical procedures. High-volume academic and non-academic hospitals in Germany, the Netherlands, Sweden, Ireland, Switzerland and France will participate in the trial. It is conducted in accordance with the principles of the Declaration of Helsinki and Good Clinical Practice Guidelines. The protocol has so far been approved by the independent ethics committee of the University Hospital of Cologne, University of Leipzig Medical Center, University Hospital rechts der Isar, University Medical Center of the Johannes Gutenberg University Mainz and the Medical Center – University of Freiburg. Any modifications to the protocol which may impact the trial will be communicated with the participating institutions and approved by the ethics committee again. The surgeon, patient and coordinating researcher will not be blinded for the allocated treatment.

### Study population

The study will evaluate patients with GEJ type II carcinoma whose tumor can be safely resected by both transthoracic esophagectomy and transhiatal extended gastrectomy. In detail, the inclusion criteria are:
Histologically proven adenocarcinoma of the GEJ type IIResectable by both transthoracic esophagectomy and transhiatal extended gastrectomy according to the local surgical investigatorPre-treatment stage cT1-4a, N0–3, M0In case of stage cT4a, curative resectability must be explicitly verified by the local surgical investigator prior to randomizationCompletion of all four cycles of chemotherapy (FLOT) preoperatively, in case of locally advanced tumors (cT3-T4 or N+)Age ≥ 18ECOG Eastern Cooperative Oncology Group (ECOG) performance status 0–2ASA < 4.Adequate bone marrow function (white blood cells > 3 × 10^9 /l; hemoglobin > 9 g/dl; platelets > 100 × 10^9 /l), renal function (glomerular filtration rate > 60 ml/min), and liver function (total bilirubin < 1.5x upper level of normal (ULN), aspartate transaminase (AST) < 2.5x ULN and alanine transaminase (ALT) < 3x ULN)Written informed consent

The exclusion criteria are:
Histologically proven adenocarcinoma of the GEJ type I and IIITumor resectable only by transthoracic esophagectomy or only by transhiatal extended gastrectomy, according to the local surgical investigatorTumor expanding more than 5 cm proximal of the GEJPositive lymph nodes only resectable by transthoracic esophagectomy (i.e. in the mid-upper mediastinum) or only resectable by transhiatal extended gastrectomy according to the local surgical investigator.Clinically significant (active) cardiac disease (i.e. symptomatic coronary artery disease or myocardial infarction within last 12 months), resulting in a left ventricular ejection fraction < 50% (determined by echocardiography)Clinically significant lung disease (forced expiratory volume in one second (FEV1) < 1.5 l/s)Pregnant women and nursing mothers

### Patient screening and chemotherapy

Figure 2 displays the trial flow. All patients will undergo evaluation in a multidisciplinary tumor board and standard tumor staging before inclusion. The staging examinations will include an endoscopy with a detailed description of the tumor localization, the classification according to Siewert and biopsy extraction for histology. To standardize endoscopic definition of Siewert type II tumors, a separate Standard Operating Procedure (SOP) for staging endoscopies has been developed. Type II tumors are defined as all tumors in which the center of the main tumor mass (half the distance between the proximal and distal edges of the main tumor mass) is 1 cm above to 2 cm below the cardia. The GEJ (or cardia) is defined as the top of gastric folds after desufflation. Tumors that expand more than 5 cm above the GEJ will also be excluded from the trial, as these are not potentially resectable by a transhiatal extended gastrectomy. In the case of severe tumor stenosis, which prevents passage of the (normal and ultra slim) endoscope and therefore an endoscopic tumor classification according to Siewert, the patient can’t be included in the trial.

**Fig. 2 Fig2:**
[figure not shown]
Trial flow chart.

A computed tomography of the thorax and abdomen will be performed to identify metastatic disease and the extension of the disease. In addition, endoscopic ultrasound to determine the tumor infiltration depth and fluorodeoxyglucose positron emission tomography with CT (FDG-PET/CT or PET) to identify distant metastases are recommended in staging, yet not mandatory. The complete preoperative work-up will further include a physical examination, medical history, demography, vital signs and laboratory tests. In patients with a history or symptoms of cardiac and/or pulmonary disease, additional cardiology consultation, echocardiography (ejection fraction > 50%) and pulmonary function tests (FEV1 > 1.5 l) will be mandatory.

For patients with locally advanced adenocarcinomas (T2 or higher, N+) multimodal treatment is the standard care according to international guidelines [12]. For T3-T4 or N+ staged patients, perioperative chemotherapy according to the FLOT protocol [13] will be obligatory for patients in the CARDIA trial. For T2 N0 staged patients, perioperative FLOT chemotherapy will be recommended, but will not be compulsory for inclusion in the CARDIA trial. It can be administered based upon the individual decision per patient. T1 N0 M0 staged patients will receive a primary resection. Perioperative chemotherapy is not part of the investigated treatment and thus does not have to be performed at the designated trial sites. If patients with locally advanced adenocarcinoma GEJ type II were fully diagnosed as described above by long-term reliable external gastroenterological collaborators of high-volume centers and secondly referred to the respective surgical department after finishing multimodal treatment with the FLOT regimen, they can also be included in the CARDIA trial.

For patients undergoing chemotherapy, restaging after four preoperative cycles will be mandatory and screening examinations will take place during restaging. Patients who do not undergo chemotherapy will receive all screening examinations during their primary staging.

### Patient inclusion and randomization

When baseline assessments and staging or restaging are completed, inclusion and exclusion criteria for the trial will be validated. Written informed consent will be obtained from all trial participants. Immediately after the patient has given his written consent to participate in the trial, randomization to one of the therapeutic arms will be performed by means of a 24/7 internet service based on permuted blocks of varying length, stratified by trial site and/or surgeon and tumor stage.

### Patient follow-up

The follow-up will include seven regular visits for check-up every three to six months with a total of 24 month after discharge. Further follow-up will be conducted as quarterly phone calls to determine survival up to 60 months after discharge. For a detailed listing of the procedures and items recorded in the eCRF for each trial visit, see Table 1. If a tumor recurrence is clinically suspected during the follow-up period, a CT of the thorax and abdomen as well as an endoscopy will be performed on indication to further document the disease-free survival. Loss-to-follow-up will be minimised by commissioning a person at the trial site to manage and encourage follow-up and providing of excellent and free medical care. We therefore assume a small attrition rate of 0.05 per year and study arm.

V0 Screening, V1 Baseline/Randomization, V2 Discharge, V3 + 1 month, V4 + 3 months, V5 + 6 months, V6 + 9 months, V7 + 12 months, V8 + 18 months, V9 + 24 months, Survival Follow-up up to 60 months – quarterly by phone. ^1^Negative serum pregnancy test during screening period for women of child-bearing age. ^2^Only in case of a clinically suspected tumor recurrence.

**Table 1 Tab1:** Visit schedule

	**V0**	**V1**	**V2**	**V3**	**V4**	**V5**	**V6**	**V7**	**V8**	**V9**	**Survival-** **Follow-up**
Demography	X										
Medical history	X										
Oncological history	X										
Tumor classification	X										
Pregnancy test^1^		X									
Inclusion / Exclusion		X									
Laboratory	X										
Biopsy	X										
Randomisation		X									
Physical examination	X		X	X	X	X	X	X	X	X	
Anamnesis	X			X	X	X	X	X	X	X	
Endoscopy	X				X^2^	X^2^	X^2^	X^2^	X^2^	X^2^	
CT/MRI	X				X^2^	X^2^	X^2^	X^2^	X^2^	X^2^	
Concomitant Medication	X		X	X	X	X	X	X	X	X	
EORTC QLQ-C30, −STO22, −OG 25-		X	X		X	X	X	X	X	X	
OP – Description			X								
Post-OP Complication			X								
Pathology			X								
Reference pathology			X								
AE/SAE			X	X	X						
Survival				X	X	X	X	X	X	X	X
EOS											or earlier for premature withdrawal

### Surgery

Patients will either receive a transthoracic esophagectomy or transhiatal extended gastrectomy depending on randomization outcome. However, the surgeon should change his/her surgical strategy if tumor-free resection margins can’t be achieved, as described below. In general, technical details of both surgical procedures are left to the individual surgeon’s preference as long as the primary goal of a complete tumor resection is achieved. This also includes all established minimally invasive surgical techniques as well as the application or support of robotic surgery devices.

### Transthoracic esophagectomy

The esophagectomy will be performed by means of a right transthoracic approach combined with resection of the proximal stomach (GEJ). Transhiatal access or access by thoraco-phreno-laparotomy is not allowed. A gastric conduit is constructed, and continuity is re-established by intrathoracic anastomosis (Ivor-Lewis). Cervical anastomosis (McKeown) is not allowed. The procedure includes a 2-field lymphadenectomy, resection of lymph node stations 1–3, 4sa, 7, 8a, 9, 11p, 11d, 12, 106 tb R, 106 rec R, 107, 108, 109 and 110 according to JGCA/JES [14, 15] is mandatory (see Fig. 3). Resection of lymph node station 106 tb L and 106 rec L are recommended, yet not mandatory (see appendix, Table 1). A total of at least 25 lymph nodes should be examined per resection according to the German S3 guidelines for gastric cancer [16]. In addition to the lymph node stations, the thoracic duct compartment also has to be resected [17].

**Fig. 3 Fig3:**
[figure not shown]
Obligatory and optional lymph node stations for lymph node dissection during transthoracic esophagectomy (A) and transhiatal extended gastrectomy (B). Lymph node stations which should be resected are marked in orange [15]., altered.

### Transhiatal extended gastrectomy

Transhiatal extended gastrectomy will be performed according to common practice at the specific hospitals. Reconstruction will be achieved by esophagojejunostomy and Jejunojejunostomy (Roux-en-Y reconstruction). For all patients randomized for transhiatal extended gastrectomy an intraoperative endoscopy is mandatory prior to transection of the tubular esophagus to ensure a tumor-free upper resection margin. In addition, an intraoperative frozen section of the oral resection margin should be performed to confirm a complete resection of the primary tumor. If a complete resection cannot be achieved, strategy must be changed and a transthoracic esophagectomy must be performed. Again, a 2-field lymphadenectomy is performed harvesting at least 25 lymph nodes, including lymph node stations 1–1-7, 8a, 9, 11p, 11d, 12a and the lower paraesophageal lymph node station 110 (see Fig. 3).

### Surgical quality control

The participating sites will be expert high-volume hospitals with a caseload of at least 15 esophagectomies and 10 transhiatal extended gastrectomies per year over the last 3 years. Only surgeons that are experienced to perform both types of surgery will be eligible to participate in this randomized trial. Surgeons who wish to use a total minimally invasive or robotic assisted approach for the esophagectomy or transhiatal gastrectomy must demonstrate that they have performed this surgical technique at least twenty times in a designated surgical team. This is to ensure quality of surgery and standardized perioperative management and to ensure a substantial allocation of patients to the trial within the designated recruitment period.

As an ongoing surgical quality assurance throughout the trial, photographs of the operating area will be taken during each surgery, showing the completeness of the lymphadenectomy. These images will be used for ongoing feedback during the course of the trial on the surgical technique. Additionally, they will be analyzed in depth if the half-yearly safety analysis by the Data Monitoring Committee (DMC) shows a reduced number of resected lymph nodes or high number of R1 resections, which could indicate insufficient surgical quality at the respective trial site.

### Pathological quality control

To ensure quality of the pathological examination, the lymph node dissection will be divided by the surgeon in single packages for each lymph node station so that the pathologist can individually analyze the different lymph node packages. However, the peritumoral stations will be marked en-bloc by the surgeon, instead of being resected in single packages, so analysis of the circumferential resection margin is not compromised. The pathological analysis of the entire surgical specimen will be carried out at each site according to a standard CARDIA trial pathology protocol. To ensure the quality of the pathological assessment of the circumferential resection margin, the resection margin samples of the respective surgical specimen will be re-analyzed by one of two reference pathologies which are located at the University Hospital of Cologne and the University Medical Center Utrecht.

### Postoperative treatment

The postoperative treatment will not differ between both treatment arms. Epidural analgesia will be performed, and other analgesia can be given according to each centers standard practice. Mobilization under supervision of a physiotherapist will start as soon as the patient is stable. Enteral feeding via a jejunostomy catheter for patients will be allowed. Patients will be discharged according to standard practice of each surgical center.

### Outcome measures

The primary endpoint is overall survival, which will be followed up until 60 months after discharge of surgery. The key secondary endpoints are complete resection (R0), post-operative complications according to the Esophageal Complications Consensus Group (ECCG) definitions [18] and scored on severity by the the Clavien-Dindo classification [19], number and localization of tumor infiltrated lymph nodes at dissection, disease-free survival, quality of life (EORTC QLQ-C30, QLQ-STO22, and QLQ-OG25 after 3, 6, 9, 12, 18, 24 months) and cost-effectiveness.

After consolidation of the EORTC questionnaires data during the course of the trail, a cost effectiveness analysis of both procedures based on direct costs and resulting QALYs will be performed and the incremental cost-effectiveness ratio will be calculated. For simplification of the process, only German sites classified as excellence centers will be included into the analysis, so that consistent national costs (e.g. DRG based, medical supply, labor costs based on tariffs) can be comparable.

### Data management and safety

The trial database will be developed and validated before data entry based on standard operating procedures at the Clinical Trial Centre Cologne (CTCC). All changes made to the data will be documented in an audit trail. The database will be integrated into a general IT infrastructure and safety concept with a firewall and backup system. Plausibility checks will be run during data entry. The CTCC Data Management will conduct further checks for completeness and plausibility and will clarify any questions with the trial sites electronically via the trial software.

The trial sites will be monitored closely to ensure patient’s safety and the quality of the data collected. Postoperative complications classified as Dindo-Clavien grade IIIb and higher (requiring surgical, endoscopic or radiological intervention under general anesthesia) or anastomosis incufficiency will be considered adverse events. A serious adverse event is defined as the death of a patient. AEs and SAEs will only be reported until three months after discharge (V4).

### Sample size calculation

The primary endpoint is overall survival. We assume a cumulative survival after 2.5 years of 45% for transthoracic esophagectomy and 30% for transhiatal extended gastrectomy (see Fig. 1c in [20]). This corresponds to a hazard ratio of 0.663. A total of 188 events need to be observed to detect this difference with the stratified log-rank test (two-sided type I error 5%, power 80%, accounting for the interim analysis according to two-sided symmetric O’Brien-Fleming type alpha-spending at 94 events). Thus, 262 patients need to be enrolled and followed up (assuming 2,5 years of accrural, 5 years of follow-up and 5% censoring per year) [21]. For the key secondary outcome R0 resection Parry et al. report percentages of 87 and 71%, respectively [20]. This corresponds to an odds ratio of 2.73. Thus, 262 enrolled patients are also sufficient to give the stratified Mantel-Hanszel test at least 80% power (two-sided type I error 5%). Before participating in the trial, each center reported possible recruitment figures based on the number of patients with GEJ type II tumors in recent years. Screening will continue until the target sample size is achieved.

### Statistical analysis

The primary analysis will be performed on the full analysis set (intention-to-treat) and comprises all patients with written informed consent and who were operated. The analysis is as assigned by stratified randomization (i.e. site or surgeon and tumor stage). The primary outcome of overall survival will be evaluated by the stratified log-rank test and is event-driven (i.e. following observation of 188 events). The hazard ratio with 95% confidence interval (CI) is estimated by stratified Cox regression. The assumption of non-informative censoring is examined using standard approaches (i.e. Kaplan-Meier curves, examining patterns of censoring across covariates and association between censoring and covariates). The key secondary outcome R0 resection rate is analyzed by comparing the corresponding odds between treatment groups with the stratified Mantel-Haenszel test. A missing assessment is counted as failure. Contingency tables of strata with “empty rows or columns” are pooled. The combined Mantel-Haenszel odds ratio with 95% CI is calculated. The potential impact of clustering associated with both interventions is addressed in a sensitivity analysis [22, 23]. The secondary outcome quality of life is averaged over 36 months (area under curve, AUC) and tested for non-inferiority of the esophagectomy arm regarding a margin of 80%. Missing values are linearly interpolated. The key outcomes overall survival, R0 resection and quality of life are tested in a fixed sequence, thus no alpha-correction is required for strong type I error control (5%, two-sided).

Subgroup analyses are done by sex, tumor stage and (essential) compliance with the protocol (i.e. per protocol analysis). Adverse events are summarized and listed by seriousness, severity and relatedness to treatment. Cumulative survival 30, 36 and 60 months following surgery is estimated by Kaplan-Meier method (with 95% CI according to Greenwood’s formula). Methods for rates and proportions are used to describe hospital mortality and the incidence of post-operative complications. A linear mixed model is fit to health related quality of life data from EORTC questionnaires QLQ-C30, QLQ-STO22, and QLQ-OG25. Cost-effectiveness is determined as the ratio ∆C/∆E where ∆C is the difference in resource use (costs) and ∆E the gain in months of life or in quality of life. The cost-effectiveness (cost per life-month gained or cost per quality-of-life-unit) will be calculated from a societal perspective.

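### The primary set is labelled intention-to-treat but leaves out randomized patients who are never operated

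*Protocol article*

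**What the plan says.** Under Statistical analysis the protocol article states: "The primary analysis will be performed on the full analysis set (intention-to-treat", and that this set "comprises all patients with written informed consent and who were operated". It adds: "The analysis is as assigned by stratified randomization". The primary test is a stratified log-rank test on overall survival at 188 events. For R0, the same section counts a missing assessment as a failure and names no other analysis set.

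The order of events is given elsewhere. Patient inclusion and randomization: "Immediately after the patient has given his written consent to participate in the trial, randomization to one of the therapeutic arms will be performed". Surgery: "Patients will either receive a transthoracic esophagectomy or transhiatal extended gastrectomy depending on randomization outcome". Study design: "The surgeon, patient and coordinating researcher will not be blinded for the allocated treatment".

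Visits and survival phone calls are timed from discharge (Patient follow-up, Outcome measures). The article describes no analysis on all randomized patients.

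**The concern.** Being operated happens after randomization, and everyone who decides on it knows the arm. A set that requires it is not an intention-to-treat set, whatever its label. One operation enters the chest and the other does not, so a patient's willingness, or a surgeon's view of fitness, may differ by arm once the allocation is known. Patients who never reach surgery plausibly have a poor prognosis. If more of them are lost from one arm, that arm looks better than it is. If that arm is esophagectomy, the error favours the hypothesis that the trial is powered to show.

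R0 is exposed in the same way. The rule that a missing assessment is a failure never reaches a patient who is already outside the set.

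**Working it through.** **1. Who leaves the set.** Taking the stated rules in order of time:

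| Patient after randomization | In the primary set? |
|---|---|
| Operated as allocated | Yes |
| Receives the other operation (declined the allocated one, or converted) | Yes, in the allocated arm |
| Explored without resection | Unclear; operated is not defined |
| No operation at all | No |

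Only the last row is certainly lost. Grouping as assigned protects against crossover among operated patients; it does not bring back those excluded.

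**2. The design figures.** Sample size calculation assumes "cumulative survival after 2.5 years of 45% for transthoracic esophagectomy and 30% for transhiatal extended gastrectomy".
- Hazard ratio: ln(0.45)/ln(0.30) = 0.663, as stated.
- O'Brien-Fleming type spending at half the information gives critical values 2.772 (interim) and 1.979 (final). With Schoenfeld's formula and 1:1 allocation (assumed, as no ratio is stated), 80% power needs 187.8, i.e. 188 events. This agrees with the article, and none of its figures is in dispute here.

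**3. Possible bias (illustration only).** The assumptions are mine:
- no true effect;
- a fraction p of patients in each arm has 2.5 times the hazard of the rest, whose hazard is −ln(0.30)/2.5 = 0.482 per year;
- exponential survival, 2.5 years of uniform accrual, 5 years in total, censoring hazard 0.05 per year;
- exclusions come only from the poor-prognosis group.

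The apparent hazard ratio is the large-sample Cox estimate among those kept. The shift of the test statistic is √(188/4) × |ln HR| = 6.856 × |ln HR|. The rejection probability uses both critical values.

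| Share of poor-prognosis patients dropped (arm A vs arm B) | p | Apparent HR (A vs B) | Shift | Two-sided type I error |
|---|---|---|---|---|
| 50% vs 50% | 5% or 10% | 1.00 | 0 | 5.0% |
| 80% vs 30% | 5% | 0.982 | 0.12 | 5.2% |
| 80% vs 30% | 10% | 0.963 | 0.26 | 5.7% |
| 100% vs 0% | 5% | 0.964 | 0.25 | 5.7% |
| 100% vs 0% | 10% | 0.929 | 0.50 | 7.9% |

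A second set of assumptions has 10% of patients with a median survival of 9 months. Excluding 5% vs 2%, 8% vs 2% and 10% vs 2% of all patients gives 0.98, 0.96 and 0.95, with errors of 5.2%, 5.8% and 6.5%.

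**4. Patient and event counts.** The 262 are enrolled patients, and the stated assumptions allow for censoring but not for exclusions. If 2%, 5% or 10% are not operated, 257, 249 or 236 remain.
- Read as 5 years in total, P(event) = 0.707. The expected events are 262 × 0.707 = 185 with no exclusions, and 182, 176 or 167 with them.
- Read as 5 years after the last patient, P(event) = 0.823. Then 188/0.823 = 228 patients suffice, and even 236 is enough.

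**5. What the correction does to power.** Suppose a fraction x is not operated and has no treatment effect. A crude dilution is ln HR × (1 − x), and the events needed for 80% power are 187.8/(1 − x)².

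| x | Diluted HR | Power at 188 events | Events for 80% power |
|---|---|---|---|
| 2% | 0.669 | 78.4% | 196 |
| 5% | 0.677 | 75.9% | 208 |
| 10% | 0.691 | 71.3% | 232 |

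**6. R0.** With non-operated patients counted as failures, the assumed 71% becomes 0.71 × 0.95 = 67% at 5% non-operated. That is below the 70% stop criterion under Interim analysis, if that criterion used the same denominator.

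**The case against.** The best defence is that few patients can be lost. Randomization comes after completed staging, or after restaging following four preoperative chemotherapy cycles, and after a check of resectability by both operations. Deterioration during preoperative chemotherapy therefore falls before randomization. The article gives no non-operation rate, overall or by arm, and equal losses leave the hazard ratio at 1.00 in the illustration. This stands, and it limits the likely size. It does not justify the rule: leaving out untreated patients is harmless only if the allocation cannot influence who is treated, and here the allocation is open.

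Four stronger readings are tempting but not supported:
- A reader might infer that anyone who refuses the allocated operation is dropped. The rule requires an operation, not the allocated one, so such a patient stays in if the other operation is done.
- A reader might infer that the primary survival clock starts at surgery, because "Cumulative survival 30, 36 and 60 months following surgery is estimated by Kaplan-Meier method" with that origin. That sentence concerns descriptive estimates. The origin for the log-rank and Cox analyses is not stated, and the full protocol may give it.
- A reader might infer that events are lost for good. The analysis waits for 188 events, so exclusions mainly delay it; a shortfall within the planned time arises only on the 5-year-total reading.
- A reader might infer that the bias must favour esophagectomy. Nothing in the article fixes its direction.

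The correction also has a real price in power, shown above.

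**Conclusion.** The point holds as a contradiction between the label and the definition of the primary analysis set. It is a stated rule, not a detail left to a fuller document, and nothing else in the article restores the excluded patients. Overall survival and R0 are compared after conditioning on a post-randomization, unblinded event.

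The size and direction of the bias cannot be derived from the article. Under the assumptions shown, unequal but not extreme losses move a null hazard ratio to about 0.98 to 0.96 and the type I error to about 5–6%. Losing every poor-prognosis patient from one arm and none from the other is an extreme case, with 0.96 to 0.93 and roughly 5.7–7.9%. With few or balanced losses the effect is negligible. The rule should still be corrected, because it governs the primary analysis and cannot be fully repaired later if the vital status of non-operated patients is not collected.

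**What to change.** - Define the primary set as all randomized patients with consent, analysed as assigned, with overall survival measured from randomization.
- Anchor survival follow-up of non-operated patients to randomization. Visits and calls now run from discharge, so a patient without surgery has no stated starting point.
- Apply the existing missing-is-failure rule for R0 to all randomized patients. State the denominator of the 70% R0 stop criterion separately, so that the two are not confused.
- Report non-operated patients and their reasons by arm.
- Keep the operated set as a sensitivity analysis, labelled modified intention-to-treat, and define operated.

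The cost is an amendment, a small amount of extra follow-up, and some dilution of the effect: crudely, 80% power at 188 events becomes about 78% at 2% and 76% at 5% non-operated. If more than a few per cent are expected not to reach surgery, the event target should be reviewed. Four patients had been enrolled at the status date in the article, so an early change would have been cheap.
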